## 6.2 Assessment of Adverse Events and Serious Adverse Events

### Assessment of Causality for Study Drugs and Procedures

The relationship of each AE to the trial medication must be determined by the site the principal investigator according to the following definitions:

**Related:** The AE follows a reasonable temporal sequence from trial medication administration. It cannot reasonably be attributed to any other cause.

**Not Related:** The AE is probably produced by the participant's clinical state or by other modes of therapy administered to the participant.

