#### **Secondary endpoint**

- Reduction in total cholesterol and triglycerides and/or effect on HDL levels
- Effect on serum glucose level related parameters (FBS, HbA1c)
- Effect on anthropometric parameters (weight, WC, HC, mid arm circumference)
- Effect on systolic and diastolic blood pressure.
- Occurrence of adverse events due to regular administration of *C. zeylanicum* extracts on liver and kidney function and the occurrence of self-reported side effects in individuals under study.

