| Adverse Reaction (AR) | 
An untoward and unintended response in a participant to an investigational medicinal product which is related to any dose administered to that participant.
 
The phrase "response to an investigational medicinal product" means that a causal relationship between a trial medication and an AE is at least a reasonable possibility, i.e. the relationship cannot be ruled out.
 
All cases judged by either the reporting medically qualified professional or the Sponsor as having a reasonable suspected causal relationship to the trial medication qualify as adverse reactions.
 |
| SAE                   | 
A SAE is any untoward medical occurrence that:
 

• results in death

• is life-threatening

• requires inpatient hospitalisation or prolongation of existing hospitalisation

• results in persistent or significant disability/incapacity

• consists of a congenital anomaly or birth defect*.

 
Other 'important medical events' may also be considered a SAE when, based upon appropriate medical judgement, the event may
                                                                                      |

|                                                       |                                                                                                                                                                                                                                                                                                                                                                                                                                                                                                                           |
|-------------------------------------------------------|---------------------------------------------------------------------------------------------------------------------------------------------------------------------------------------------------------------------------------------------------------------------------------------------------------------------------------------------------------------------------------------------------------------------------------------------------------------------------------------------------------------------------|

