|                                                       | jeopardise the participant and may require medical or surgical intervention to prevent one of the outcomes listed above.                                                                                                                                                                                                                                                                                                                                                                                                  |
| Serious Adverse Reaction (SAR)                        | An AR that is both serious and, in the opinion of the reporting Investigator, believed with reasonable probability to be due to one of the trial treatments, based on the information provided.                                                                                                                                                                                                                                                                                                                           |
| Suspected Unexpected Serious Adverse Reaction (SUSAR) | 
A serious adverse reaction, the nature and severity of which is not consistent with the Reference Safety Information for the medicinal product in question set out:
 
 
• in the case of a product with a marketing authorisation, in the approved summary of product characteristics (SmPC) for that product
 
• in the case of any other investigational medicinal product, in the approved investigator's brochure (IB) relating to the trial in question.
 
 |

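### Section 6.2 sets a stricter test for a 'Related' adverse event than section 6.1 sets for an adverse reaction, and its two categories do not cover every event

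*Protocol*

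**What the plan says.** Section 6.1 defines an adverse reaction by a low bar: "a causal relationship between a trial medication and an AE is at least a reasonable possibility, i.e. the relationship cannot be ruled out". It adds that a case judged by the reporting professional or by the sponsor as "having a reasonable suspected causal relationship to the trial medication qualify as adverse reactions". For a serious adverse reaction it requires an adverse reaction that is serious and is "believed with reasonable probability to be due to one of the trial treatments".

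Section 6.2 then gives the working rule. The relationship of each event "must be determined by the site the principal investigator according to the following definitions". 'Related' has two parts: "The AE follows a reasonable temporal sequence from trial medication administration", and "It cannot reasonably be attributed to any other cause". 'Not Related' begins "The AE is probably produced by" and names the participant's clinical state or other therapy. There is no third category.

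Section 6.3 makes the relatedness judgement a CRF item, next to an item for any other suspected drug or device. Section 4.2, repeated in the synopsis, words part of the secondary safety endpoint as "Occurrence of adverse events due to regular administration of" the extract. The matching objective in section 2 and the measure in section 4.3 refer to possible liver and kidney effects and self-reported side effects, and do not restrict these to events judged to be caused by the product.

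**The concern.** The two sections ask different questions. Section 6.1 asks whether the capsule can be excluded as a cause. Section 6.2 asks whether every other reasonable cause can be excluded. Many events will be answered differently.

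The protocol itself expects non-specific events. Section 1.3 names dyspeptic symptoms from an earlier phase I study, and section 4.4.2 foresees intolerance when capsules are taken before meals. Section 3.2 excludes ALT and AST only above three times the upper limit of normal, so some participants may enter with raised enzymes, which offers a ready alternative explanation for a later rise. The CRF item on other suspected drugs shows that competing causes are anticipated.

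At stake is the attributed safety count. Because investigators make this judgement while the trial runs, an analysis plan written later cannot simply recover what they would have recorded under the other threshold.

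**Working it through.** The protocol gives no expected reaction rate and no figure for this point, so there is nothing to reproduce or compute. The check sets the definitions side by side.

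**Inputs**

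- Reaction (6.1): the causal link is a reasonable possibility and cannot be excluded.
- Related (6.2): timing fits, and no other cause to which the event can reasonably be attributed.
- Not Related (6.2): another source is probable.

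**Events with plausible timing for which the capsule cannot be excluded**

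| Group | Alternative cause | Under 6.1 | Under 6.2 |
|---|---|---|---|
| a | None that is reasonable | Reaction | Related |
| b | Reasonable, but not probable | Reaction | Neither label fits |
| c | Probable | Reaction | Not Related |

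**Reasoning**

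1. Every event in group a counts under both sections. If timing fits and no other reasonable cause exists, the capsule cannot be excluded. So 'Related' under 6.2 is a subset of 'reaction' under 6.1.
2. Groups b and c are reactions under 6.1 and are not 'Related' under 6.2. If n denotes the number of events in each group, then n(Related, 6.2) = n(a) ≤ n(a) + n(b) + n(c) = n(reaction, 6.1). Equality holds only if groups b and c are empty.
3. Group b has no valid entry under 6.2. An investigator faced with two labels must pick one against its definition, and sites may choose differently. Even if all of group b were entered as 'Related', the count would be n(a) + n(b), still no larger than the 6.1 count.
4. Section 6.2 is the only attribution rule that investigators are told to apply, and section 6.3 puts the result on the CRF. Section 4.2 counts events due to the extract and gives no other rule for deciding this. The attributed part of that endpoint therefore most naturally takes the 6.2 label.
5. Sections 4.4.2 and 4.5 keep investigators blinded, so the same rule acts on events in both arms.

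The direction is thus fixed. The size depends on n(b) and n(c), about which the protocol says nothing.

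**The case against.** The strongest reply is that this affects a label and little else. Sections 4.4.3 and 4.4.4 record all adverse events whatever their cause, and section 6.3 requires every SAE to be reported within 24 hours without a relatedness filter. Liver and kidney tests are scheduled for everyone at Visits 1 and 5, and self-reported side effects need no causality label. Section 4.2 does not cite section 6.2, so the link between them is an inference. No analysis in section 8 uses relatedness. All of this stands and limits the point to the attributed count.

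Several stronger readings are tempting, and the protocol does not support them:

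- **That any conceivable alternative cause blocks 'Related'.** Section 6.2 says the event cannot *reasonably* be attributed elsewhere, so a remote alternative does not block the label.
- **That three thresholds conflict.** The wording for serious adverse reactions is a further condition on an event that is already an adverse reaction. It is nested within the 6.1 definition and does not rival it.
- **That SAR and SUSAR classification is suppressed.** This is possible if the 6.2 label feeds that chain, but no section says it does, and section 6.1 also lets the sponsor judge a case to be a reaction. Equally, no procedure is given for the sponsor's judgement, and nothing says it overrides the CRF entry, so it does not remove the inconsistency.
- **That the comparison of arms is biased, or that attributed events mean nothing under placebo.** Blinded investigators attribute events to the capsule in both arms under one rule, which does not by itself favour either.
- **That a given fraction of reactions is lost.** No figure in the protocol supports one. The exclusions in section 3.2, among them lipid-lowering drugs, herbal supplements and alcoholic liver disease, remove some competing causes.

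It can also be said that safety definitions often sit in the analysis plan. That holds for analysis detail, but not for a causality rule that investigators apply during conduct and that the protocol states in two incompatible ways.

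**Conclusion.** The point holds in limited form. Sections 6.1 and 6.2 contradict each other on when an event counts as caused by the product, and the 6.2 categories are not exhaustive. Followed as written, 6.2 gives a count of attributed events that is equal to or lower than under 6.1, in both arms, by an amount that cannot be derived.

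For the CRF label, the conclusion rests only on the protocol's definitions. For the secondary endpoint, it also assumes that events due to the extract are identified by the 6.2 label, for which the protocol offers no alternative. The primary LDL comparison is untouched. The change is worth making because it is cheap and because the affected judgements are made during the trial.

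**What to change.** - **Section 6.2:** define 'Related' by the 6.1 threshold, so that a causal link which is at least a reasonable possibility and cannot be excluded is enough. Define 'Not Related' as every other adverse event, so that each event has exactly one label.
- **Sections 6.1 and 6.2:** state that classification as an adverse reaction or serious adverse reaction follows from this label, and how a sponsor judgement that differs from the investigator's is recorded.
- **Section 4.2 and the synopsis:** bring the safety endpoint into line with the section 2 objective and section 4.3 by comparing all adverse events and the liver and kidney changes between randomised arms, with related events reported as a subset.

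The cost is protocol wording and CRF guidance. No visit, test or sample size changes. The downside is that more events will be labelled related in both arms, so the label will be less specific. The comparison of all events by randomised arm does not depend on it.

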## **Assessment of Severity**

Intensity/Severity of an AE will be graded as mild, moderate, or severe by the investigator based on her/his medical judgment and the following guidance:

**Mild:** asymptomatic or mild symptoms; clinical or diagnostic observations only; intervention not indicated.

**Moderate:** minimal, local or non-invasive intervention indicated; limiting age-appropriate instrumental activities of daily living (e.g. preparing meals, shopping for groceries or clothes, using the telephone)

**Severe:** medically significant but not immediately life-threatening; hospitalization or prolongation of hospitalization indicated; disabling; limiting self-care activities of daily living (e.g. bathing, dressing and undressing, feeding self).

### **6.3 Investigator Requirements and Instructions for Reporting Adverse Events and Serious Adverse Events**

All SAEs must be reported on the SAE reporting form to the principal investigator within 24 hours of the Central Study Team becoming aware of the event. SAEs that are reported late must be accompanied by an explanation for this. The principal investigator will perform an initial check of the report and request any additional information from the Central Study Team.

The following information will be reported on the CRF: description, date of onset and end date, severity, assessment of relatedness to trial medication, other suspect drug or device and action taken. Follow-up information should be provided as necessary.

Site investigator/s will adhere to local ethical requirements of safety reporting. Such AE/SAE conditions will be followed up by the investigator until the issue is resolved.

## 7. DATA MANAGEMENT

Data collection: data collection will be carried out by trained research coordinators, using a standardized case record form, at screening (Visit ‘1’), randomization (Visit ‘2’) and during each monthly follow up visit (Visit ‘3’ and ‘4’) and EOS (Visit ‘5’). After filling out the CRF, data collection will be performed according to the standard operating procedures (SOPs). Storage: data will be entered into a local database by a minimum number of dedicated staff and saved in a dedicated computer with password protection.

## 8. STATISTICAL CONSIDERATION

### 8.1 Sample size

The sample size was calculated assuming that the IMP would reduce total cholesterol by 10 mg/dL using below formula [31]. Assuming a standard deviation of 40 for total cholesterol and a correlation of 0.9 between the baseline and three months measurement a sample size of 64 per group would give 90% power at a significance level of 0.05. Expecting a 15% dropout rate the final sample size required will be 150 (75 per arm).

$$N \approx 4\sigma^2(1 - \rho^2)(z_{1-\frac{\alpha}{2}} + z_{1-\beta})^2/\Delta^2$$

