#### 3.1 Inclusion Criteria

Subjects will be eligible if they meet all the following inclusion criteria:

- Age between 18-70 years
- LDL level; between 100 and 190 mg/dL ( $100 \text{ mg/dL} \leq \text{LDL} < 190 \text{ mg/dL}$ )

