### 4.2 Primary and secondary endpoints

#### **Primary endpoint**

The primary endpoint is:

- Reduction in LDL levels after three months of treatment.

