#### **Primary effectiveness measures**

- Change in LDL levels from baseline to final follow-up at three months post randomization.

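### The 90% power in section 8.1 is for total cholesterol, a secondary endpoint; the protocol states no power for LDL, its primary endpoint

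*Protocol*

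**What the plan says.** The primary endpoint in section 4.2 is "Reduction in LDL levels after three months of treatment". Section 4.3 gives the matching effectiveness measure: "Change in LDL levels from baseline to final follow-up at three months post randomization". The synopsis and section 2 name LDL in the primary objective as well. Total cholesterol is listed among the secondary endpoints, both in the synopsis and in section 4.2.

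Section 8.1 holds the only sample-size and power statement. It begins "The sample size was calculated assuming that the IMP would reduce total cholesterol by 10 mg/dL using below formula" and continues "Assuming a standard deviation of 40 for total cholesterol and a correlation of 0.9 between the baseline and three months measurement". From these inputs it concludes that "a sample size of 64 per group would give 90% power at a significance level of 0.05", and then "Expecting a 15% dropout rate the final sample size required will be 150 (75 per arm").

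Section 8.2 also names total cholesterol as the outcome compared by ANCOVA. The statistical paragraph of the synopsis describes the same ANCOVA for LDL.

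**The concern.** The planning difference, the SD and the correlation all belong to one variable, and the primary analysis is of another. A power statement holds only for the variable whose difference and variability went into it, so the 90% is a property of a secondary endpoint. The protocol does not say that the LDL inputs are taken to be the same, and it gives no LDL inputs from which a reader could work out the power.

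The sample-size paragraph is where an ethics committee or other reader learns whether the trial is large enough for its main question. Here it answers a different question. Because 8.2 carries the same variable, section 8 as a whole does not match the endpoint sections, and a later reader could dispute which lipid the trial was planned around. A separate statistical analysis plan would not settle this, since the protocol itself fixes the sample size and does so on the wrong variable.

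**Working it through.** **1. Reproduce the stated figure (total cholesterol).** Inputs from section 8.1: difference 10 mg/dL, SD 40, correlation 0.9, two-sided alpha 0.05 (the formula uses the 1 − α/2 quantile), power 90%.

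- N = 4σ²(1 − ρ²)(z₀.₉₇₅ + z₀.₉₀)²/Δ² = 4 × 1600 × 0.19 × (1.960 + 1.2816)²/100 = 127.8, which is 63.9 and so 64 per group. This matches.
- Residual SD = 40 × √(1 − 0.81) = 17.44. Power at 64 per group is 90.05% by the normal approximation (89.6% from the noncentral t with 125 degrees of freedom).
- Dropout: 64/0.85 = 75.3 per arm. The stated 75 leaves 75 × 0.85 = 63.75 analysed per arm and 89.9% power, so the rounding is immaterial.

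The calculation is correct for the variable it uses.

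**2. Look for the LDL equivalents.**

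| Quantity | Total cholesterol (secondary) | LDL (primary) |
|---|---|---|
| Difference to detect | 10 mg/dL | not stated |
| SD | 40 | not stated |
| Baseline-to-3-month correlation | 0.9 | not stated |
| Power | 90% | not stated |

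No single LDL power can therefore be computed from the protocol. If LDL happened to share all three inputs, power would again be 90%, but the protocol does not say so.

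**3. Illustrate how far the power could move.** The LDL inputs below are assumptions, not figures from the protocol. With 64 analysed per arm, residual SD s = SD × √(1 − ρ²) and power ≈ Φ(Δ/(s√(2/64)) − 1.960).

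| Assumed LDL difference, SD | ρ = 0.7 | ρ = 0.8 | ρ = 0.9 |
|---|---|---|---|
| 10 mg/dL, SD 30 | s = 21.4, 75% | s = 18.0, 88% | s = 13.1, 99% |
| 6.5 mg/dL, SD 26 | s = 18.6, 50% | s = 15.6, 65% | s = 11.3, 90% |

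The second row has the same ratio of difference to SD as section 8.1 (6.5/26 = 10/40 = 0.25). Its powers are therefore also those of the protocol's own total cholesterol inputs at each correlation. Section 8.1 gives a reference for the formula but none for the value 0.9.

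**4. What 64 per arm can detect.** At 90% power the detectable difference is (1.960 + 1.2816) × s × √(2/64) = 0.573 s. With s = 17.44 this is 9.99 mg/dL. For LDL it depends on a residual SD that the protocol does not give.

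**The case against.** The strongest reply is that the mismatch may do no harm. LDL could have a smaller SD than total cholesterol, and on some inputs the power for LDL exceeds 90%: the illustration above reaches 99%. Enrolment, conduct and the validity of the randomised LDL comparison do not depend on the planning text. All of this stands. It limits what can be said about the trial's actual power, but it does not supply the missing figure.

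Three stronger readings are tempting and are not supported.

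- **The entry window shows a loss of power.** Section 3.1 requires "LDL level; between 100 and 190 mg/dL", and a reader might infer that this narrow range lowers the correlation and hence the power. ANCOVA power depends on the residual SD. Take a normal baseline with mean 120 to 140, SD 40 and correlation 0.9, and cut it to 100–190. The baseline SD falls to 23.0–23.8 and the correlation to 0.77–0.78, but the residual SD stays at 17.4, so power for a 10 mg/dL difference stays at about 90%. Nor is 90/√12 = 26 a ceiling on the baseline SD; it is simply the value for an even spread over the window.
- **The trial is underpowered for LDL.** The lower figures in the illustration rest on assumed inputs. Section 1.3 cites a study in people with type 2 diabetes with LDL falls of 7–27% beside total cholesterol falls of 12–26%. At the window's limits, 7% is 7 to about 13 mg/dL, so an effect of 6.5 mg/dL lies just below that range. The cited study is background and not a planning input, so it does not settle the LDL difference either way.
- **A null LDL result could not be interpreted.** It could: the confidence interval from the ANCOVA would show which LDL differences are excluded, whatever power was planned.

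**Conclusion.** The point holds as an inconsistency between the sample-size section and the primary endpoint. The arithmetic is not at fault. The 90% applies to a secondary endpoint, and the protocol gives no LDL difference, SD, correlation or power. Nothing elsewhere in the protocol repairs this.

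The effect on power is of unknown direction. On the assumed inputs shown, power for LDL at 64 analysed per arm runs from about 50% to 99%. That range indicates sensitivity to the missing inputs and is not an estimate for this trial. The reproduction of 64 per group and the absence of LDL inputs rest on the protocol alone.

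**What to change.** Rewrite section 8.1 for LDL. State the LDL difference to detect, and either the residual SD or the SD with the baseline-to-three-month correlation, as expected in the enrolled population and each with its source. Keep the total at 150. Restate the power that 64 analysed per arm gives for LDL, with a short table over a range of correlations. If the total cholesterol calculation is retained, label it as power for a secondary endpoint.

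In the same edit, reconcile section 8.2, which names total cholesterol, with the synopsis, which names LDL, so that the primary ANCOVA is described for one variable throughout.

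The cost is one rewritten paragraph, one corrected sentence and a short calculation. No further participants or procedures are needed. The drawback is that the restated power may be less favourable than 90%.
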